### Approach to adaptations during the project

This is a quality improvement project and adaptations according to local need are expected. We recognise that there may be delays in securing agreement from participating sites, and difficulties with Information Technology. There are a number of different Laboratory Information Management Systems (LIMS) in use in the UK, and only one of these (“Telepath”) has currently been interfaced with the project software.

We will have a total of four steps, each of six months duration. In summer 2015 we performed an initial randomisation (using random number generation) to an intervention start-time. Due to delays and uncertainties with candidate sites, we performed a first randomisation to select the four centres in the first intervention step (from ten available at that time). A second randomisation to allocate the remaining 15 centres to the second, third and fourth randomisation steps was then performed in late 2015.

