### Outcome measures

Outcomes will be examined at renal centre level and, if necessary, laboratory level using Geographic Information Systems to map patients to laboratories. Routinely collected baseline data will be provided by the UK Renal Registry and baseline referral rates supplied by participating centres.

The UK Renal Registry (UKRR) routinely collects and publishes treatment and clinical performance data for all adult renal centres in the UK [10]. As part of this, it routinely receives an extract of data on numbers of patients starting dialysis in each renal centre and timeliness of referral.

Our primary quantitative outcome measure is the incidence of late presentation for renal replacement therapy, defined as any patient first seen by renal services within 90 days of starting renal replacement therapy. These data will aggregate into six-month time periods, two per calendar year (Jan to June; July to December).

The following secondary outcomes will be studied:(i.)the use of temporary vascular access for starting dialysis(ii.)latest eGFR measurement, within two weeks before start of RRT(iii.)mortality at 6 months from start of RRT in new RRT patients(iv.)the incident rate of ESKD, measured annually.

All outcomes measures are routinely collected by the UK Renal Registry with the exception of vascular access, which is collected annually as part of the Registry’s Multisite Dialysis Access Audit.

The number of new patient referrals (per quarter) will be recorded as a balancing measure. These data are readily extractable from renal centre appointment systems.

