#### Analysis of primary outcome

Analysis of changes in risk of late-referral will be performed using a mixed-effects logistic regression, as a patient level analysis, with the clustering at renal centres being accounted for by fitting renal centre as a random effect. The primary outcome response will be binary (patient referral <90 days = 1, patient referral ≥90 days = 0). It is expected that the risk of being late referred should decrease with the intervention. The odds ratio estimate of the risk of being late-referred for the treatment effect (intervention versus control) with 95% confidence interval will be presented (model 1). Analysis will be adjusted by time-period or step (model 2), and individual patients’ characteristics such as age at start of RRT, gender, primary renal diagnosis, ethnicity and deprivation score (model 3). Due to the nature of the intervention it is anticipated that its impact on late referral will change over time, as the risk of being late-referred is expected to decrease after the intervention is implemented, and possibly more so with time from start of intervention (we expect a cumulative effect, at least up to a certain point). Therefore we aim to explore for possible interaction between time and treatment effect (model 4).

The results from model 2 will be considered the primary result, as our intention is to determine if changes in the risk of being late-referred for RRT are related to the intervention and not to an independent time-trend.

Power calculations for the primary outcome have been derived on Stata [11], based on UKRR data returns from twelve candidate renal centres. The UKRR reached complete coverage of the UK in 2007 and data on adult incident RRT patients have been routinely collected since then. Therefore we are able to use data on new incident patients commencing RRT before the project started, and we plan to include in the analysis the population of RRT incident patients in 2013–14 for the participating centres. We therefore used the formula published by Woertman, which can accommodate the inclusion of additional historic data [12]. The percentage of late referral in these twelve centres ranged from 9 to 35%, with an average of 18%. With power set at 80%, alpha at 0.05 and intra-class correlation (ICC) at 0.05 (based on analysis of UKRR 2013 data) we should be able to detect a reduction in late presentation rate from 18 to 11%.

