Given the extreme financial constraints under which the UK National Health Service is currently operating, it is imperative to perform a robust evaluation of any quality improvement intervention. The proposed evaluation will ensure that the project is delivering improvement as expected and therefore represents an appropriate use of scant resource. It will also help to inform the aformentioned sites where the eGFR graph intervention is being introduced routinely outside the project [20].

The project has limitations and challenges. We recognise the complexities inherent in a stepped wedge approach, from both an analytical and operational perspective. The follow up is quite short and we do not have time to have a transition phase immediately following implementation of the intervention. We will not be performing interim analyses and believe that it is very unlikely that anything in these analyses would give good grounds to change the duration of the steps. However the number and duration of steps will be reviewed by a project Evaluation Advisory Board, if needed, as dictated by operational and logistical issues. There are several laboratory IT systems in operation across the UK and the need for the eGFR graph system to work across multiple platforms may impact upon the project time-lines. Delays will be mitigated by over-recruitment and pre-allocation of intervention start time at the point of formal expression of interest.

The UK pathology laboratory environment is evolving. The Audit Commission called for pathology services to be re-organised in 1993, but changes have been slow to be implemented. “Hub and spoke” models were recommended in Lord Carter’s 2008 review of pathology services, where routine (including GP) work is consolidated into large hubs. This model offers both opportunities and threats. Consolidation of high volumes of GP samples into a single laboratory/laboratory cluster will allow a single site deployment of our intervention to reach far larger numbers of surgeries. The risks are that historic pathology data may not be transferred to new systems, preventing the retrospective charting of renal function, and that there may be pathology reorganisations at participating sites within the project lifespan.

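### Patients starting RRT in the first 90 days after go-live are coded as intervention although the graphs cannot change their late/not-late status, which shrinks the model 2 effect to about 0.63 of its size; the power statement ignores this

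*Protocol article*

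**What the plan says.** Under Outcome measures, late presentation is "defined as any patient first seen by renal services within 90 days of starting renal replacement therapy", and the data are grouped into half-years. Table 1 (Project design) codes each centre 0 or 1 by half-year, with 1 from the first half-year of its step and no transition cell.

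Under Analysis of primary outcome, the model is a patient-level mixed logistic regression with a random centre effect. Model 2, with one treatment term adjusted for period or step, is named as the primary result. The same section expects the effect to build up with time since the start of the intervention, but leaves that to an exploratory interaction model (model 4).

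The power statement, at 80% power, alpha 0.05 and ICC 0.05, is that "we should be able to detect a reduction in late presentation rate from 18 to 11" per cent. It is "based on UKRR data returns from twelve candidate renal centres" and on this method: "We therefore used the formula published by Woertman, which can accommodate the inclusion of additional historic data". It mentions no lag and gives no number of patients per centre and period.

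The Discussion lists as a limitation: "The follow up is quite short and we do not have time to have a transition phase immediately following implementation of the intervention".

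**The concern.** Take a patient who starts RRT on day d after go-live, with d below 90. That patient is not late only if first seen at least 90 days before RRT, which is before go-live. A graph sent afterwards cannot create that visit. So for roughly half of each centre's first intervention half-year, the outcome cannot respond to the intervention, yet those patients carry the code 1.

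This looks minor, because the window holds only about one seventh of all intervention patient-time. It is not minor in a period-adjusted stepped-wedge analysis, where the treatment contrast comes largely from the half-year just after each switch. At stake are the size of the primary odds ratio, which is pulled towards 1, and the meaning of the power claim, which assumes a full effect from day one that the outcome definition rules out.

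**Working it through.** **Inputs from the protocol.** Late presentation 18% and 11%; alpha 0.05 (taken as two-sided); ICC 0.05; ten half-years, of which five (2013 to mid-2015) precede the first switch; four steps. Table 1 shows 18 centres (4, 5, 5, 4). The text on adaptations gives 4 + 15 = 19, taken here as 4, 5, 5, 5. The power inputs came from 12 centres, taken as 3 per step.

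**Assumptions.** Go-live falls at the start of the half-year, as Table 1 codes it. RRT starts are spread evenly over time. There is no effect in the first 90 days and the full effect afterwards. The model is linear: random centre intercept, fixed period effects, one 0/1 treatment term, and variance averaged over 18% and 11%. This approximates the planned logistic model.

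**1. The plan's own figure.** Individual randomisation needs 396 per arm, 792 in total. Because patients per centre and half-year are not stated, the 80% cannot be checked directly; one can only solve for the size that gives it. The Woertman design effect with five baseline periods needs 19.8 (19 centres), 20.9 (18) or 31.7 (12). The linear model on Table 1 needs 19.8, 21.3 and 31.0. These agree, so the 80% is not shown to be wrong on its own terms, that is, with an immediate full effect.

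**2. Unexposed share of the first intervention half-year.** 90/182 = 0.495.

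**3. Simple average.** With 19 centres there are 4×5 + 5×4 + 5×3 + 5×2 = 65 intervention centre-periods, of which 19 are first periods. The unexposed share is 19 × 0.495 / 65 = 0.145, so a plain average keeps 0.855 of the effect. Power would be Φ(0.855 × 2.80 − 1.96) = Φ(0.43) = 67%.

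**4. What model 2 estimates.** The period-adjusted estimator puts about three quarters (0.75) of its net treatment weight on the first period after the switch. Expected fraction of the full effect: 1 − 0.495 × 0.75 = 0.63. The exact results are 0.624 (18 centres), 0.631 (19) and 0.634 (12). A 7-point effect is therefore estimated as 0.63 × 7 = 4.4 points.

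**5. Power = Φ(fraction × 7/SE − 1.96).**

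| Setting | Immediate full effect | With the 90-day lag, coded as in Table 1 |
|---|---|---|
| Size set to give 80% (7/SE = 2.80) | 80% | Φ(0.63 × 2.80 − 1.96) = about 42% |
| 19 centres, 31 per half-year | 94% | about 60% |
| 19 centres, 40 per half-year | 98% | 70% |
| 19 centres, 50 per half-year | 99% | 79% |

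If 7 points is read as the average over all intervention patients, the full effect is larger by 1/0.855. Calibrated power is then Φ(0.631/0.855 × 2.80 − 1.96) = Φ(0.11) = about 54%.

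**6. Sensitivity.** With 19 centres at 20 per half-year, an ICC of 0.01 or 0.10 gives a fraction of 0.65 or 0.63, and power of 81–82% falling to 44–45%. In the calibrated case, leaving out the 2013–14 data lowers the fraction to about 0.57 and power to about 36%.

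**7. Alternatives, calibrated case.** Coding the 90 days as control with quarterly period effects gives about 80%. Dropping the 90 days gives about 70%.

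**The case against.** - **A reader might infer that the stated power is simply halved.** The protocol does not support that as a fact. The fall to about 42% holds only if centre size is exactly what yields 80%. If the 80% was worked out for twelve centres, about 31 starters per half-year are implied; nineteen such centres start at 94% and end at about 60%. This stands. The firm result is the attenuation, which barely moves with centre size.
- **The 7 points may not be a mature effect.** The protocol states a detectable contrast and does not say that it applies only after a lag. This also stands, and on the other reading calibrated power is about 54%. That is still well short of 80%.
- **The issue is disclosed, and model 4 addresses it.** The limitation is stated and a build-up of effect is anticipated, so the authors were aware. But the limitation changes neither coding nor power, and model 4 is exploratory while model 2 is the primary result.
- **Coding by allocated period gives a pragmatic roll-out effect and cannot create a false positive.** This is a fair choice of target, and dilution does run towards no effect. Yet model 2 does not return the average roll-out effect: under this lag that average is about 0.86 of the full effect, while model 2 gives about 0.63.
- **A reader might also infer that the first step was coded as exposed before it was randomised**, from "In summer 2015 we performed an initial randomisation" set against coding from July 2015. Summer includes June and July, and no go-live dates are given, so this shows no error.
- **Graphs could shift RRT timing** and so slightly alter who starts within the window. True, but they cannot change when such a patient was first seen before go-live.

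**Conclusion.** The point holds. The outcome definition and the Table 1 coding together place patients whose outcome cannot respond in the intervention arm, in the cells that carry most weight in the primary model. Model 2 then estimates about 0.63 of the effect that exists once graphs can act. This rests on the Table 1 layout, ICC 0.05, go-live at the start of each half-year, a full effect from day 90 and a linear approximation.

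Ninety days is a minimum lag, since laboratory review, GP action and the clinic appointment add to it, so the true attenuation is probably greater. The loss of power is real but cannot be given as one number without the centre size. What can be said is that the 18% to 11% statement assumes an immediate full effect, which the outcome definition excludes.

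**What to change.** 1. In the primary model, code a patient as exposed only if RRT started more than 90 days after the centre's scheduled (randomised) go-live date, and adjust calendar time by quarter. Anchoring on the scheduled date preserves the randomisation.
2. Prespecify two sensitivity analyses: the as-allocated half-year coding of Table 1, and an analysis that drops the 90-day window.
3. Restate the power with this lag, giving patients per centre and period, the number of centres and a range over centre size.
4. Amend the Discussion sentence on the transition phase to say that the lag is handled in the analysis, so no extra calendar time is needed.

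**Cost.** This is a change of wording. The analysis is already at patient level, and the pre-RRT eGFR and six-month mortality outcomes already need each patient's RRT start date. Lagged coding loses no patients. The real trade-off is in meaning: the primary estimate becomes the effect once graphs can act, not the roll-out effect from day one, and some dilution remains because 90 days is only the minimum lag.

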## Abbreviations

ADB: Advisory and dissemination board
ASSIST-CKD: A programme to spread eGFR graph surveillance for the early identification, support and treatment of people with progressive chronic kidney disease
CKD: Chronic kidney disease
eGFR: Estimated glomerular filtration rate
ESKD: End-stage kidney disease
LIMS: Laboratory information management system
PPT: Patient project team
RRT: Renal replacement therapy
